## Type and Duration of Follow-up of Subjects after Adverse Events

All AEs will be followed up until resolved or stabilized. The medical care provided will be decided by the CI and clinical personnel involved in the study to provide the best outcome and recovery for the study participant. In general, all AEs will be recorded at each of the scheduled interim visits until AE are resolved or stabilized.

## Halting Rules

Study product administration in the trial will be halted for expedited ISM/SMC review if, during the 7 days after product administration, any of the following occur:

• One (1) or more participants experiences an SAE that is unexpected and associated with study product administration

• 10% or more of the participants enrolled to date experience a severe (grade 3) study product associated fever

• 10% or more of the participants enrolled to date experience a severe (grade 3) study product associated local redness or induration;

• 10% or more of the participants enrolled to date experience a severe (grade 3) study product associated subjective reaction (pain, headache, malaise or myalgia), the severity of which is corroborated by study personnel

• One (1) or more participants experience a study product -associated bronchospasm or other anaphylactic response

• One (1) or more participants experience a study product-associated allergic event or vaccine site ulceration, abscesses or necrosis

The trial will be halted at any time if there is:

• Any patterns of laboratory values or clinical symptoms that the CI considers to be a significant safety issue for participants or any clinical symptoms of rheumatic carditis and/or rheumatic fever as defined by Jones criteria. (see Appendix G).

• ECG or ECHO abnormality such as:

- Increase in valvular regurgitation to greater than mild severity;
- Development of mitral regurgitation with an EROA of 20mm2 or >10mm2 increase from the baseline study;
- An absolute increase in effective regurgitant area of 10mm2 compared to baseline;
- Development of mitral regurgitation with an EROA > 20 mm2 and

echocardiographic criteria of probable RHD will require notification of the appropriate regulatory bodies as associated SAE.

- Any abnormal valve leaflet thickening (subjective);
- Worsening left ventricular systolic function (ejection fraction of < 50%);
- Left ventricular dilatation (based on LV diameter > upper limit of reference ranges for LV end diastolic diameter (LVEDd) indexed for body surface area (Females 24-32 mm/sqm; Males 22-31mm/sqm);
- Significant right ventricular dysfunction;
- Evidence of pulmonary hypertension (estimated RVSP > 40mmHg);
- Development of more than trivial pericardial effusion;

Subsequent reviews of serious, unexpected and related AEs by the ISM, SMC, QIMR-HREC, QIMR or TGA may also result in suspension of further study product administrations. On initiative by the TGA and the sponsors, suspension may be applied for any additional enrollment or administration of the investigational vaccine for the entire study.

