## Safety Oversight (ISM plus SMC)

The Safety Oversight in this study will be under the direction of both Independent Safety Monitor (ISM) and the Safety Monitoring Committee (SMC).

Independent Safety Monitor

The ISM is a physician with relevant expertise, whose primary responsibility is to provide independent safety monitoring in a timely fashion. Participation is for the duration of the study and the ISM is appointed by the sponsor. The ISM should be able to access participant records readily in real time. The primary focus of the ISM is to independently review serious adverse events that may be associated with product and adverse events of special interest. The ISM should investigate those events considered serious and unexpected. Clinical and laboratory data, clinical records and other study-related records should be made available for ISM review. It is the responsibility of the CI to ensure that that the ISM is appraised of all new safety information relevant to the study product and the study. This includes providing the ISM with a copy of the Clinical Investigator’s Brochure (CIB) in advance, as well as promptly providing all CIB revisions and all other safety information issued by the sponsor that is received by the CI. The ISM should receive all protocol revisions and may receive other documents related to the study.

The ISM will be in communication with the CI at the enrollment site and the SMC chair for any event that needs further evaluation.

The ISM together with the clinical investigator (CI) will be also involved in the review of all reactions including the solicited events that have occurred within the observation window for the two participants that will initially receive the study product. The ISM will also be involved in the decision making by SMC on whether the remaining participants will receive the first dose.

The ISM will not be directly involved with the trial and is not under the CI’s supervision and has no financial, intellectual, proprietary or professional interest in outcome of the trial.

Safety Monitoring Committee

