The SMC will be composed of the ISM, an infectious diseases physician, a physician with expertise in clinical trials or vaccine studies and a cardiologist. The safety of each dose of the vaccine candidate through Day 28 in the 20 participants will be evaluated by the SMC following a review of a clinical and laboratory safety data package. The SMC will also review the recorded AEs and SAEs. The SMC makes recommendations to the sponsor. These recommendations are approved by the SMC chair who signs a letter of recommendation that is sent to the CI.

In regards to the safety review of the first dose, the SMC will provide recommendations to the sponsor for administration of the second dose. These recommendations will be communicated to the CI, PI and QIMR-HREC prior to administration of the second dose. There will also be a safety review by the SMC after the second dose with recommendations regarding the continuation or modification of the study.

Additionally, the SMC will meet to assess any events that trigger the halting rules or as needed to provide a recommendation and findings to QIMR-HREC, the PI and the CI, in accordance to the approved SMC charter.

Whether at a scheduled or unscheduled meeting, the SMC will consider safety signals to determine whether or not they can recommend that the study continue.

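### Between SMC approval and the first Dose 2, and beyond day 7 after an early Dose 2, an unexpected, associated SAE outside the rheumatic and ECG/ECHO triggers halts dosing only if someone decides that it should

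*Protocol*

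**What the plan says.** Section 9.5 of the protocol contains two lists.

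- The first begins "Study product administration in the trial will be halted for expedited ISM/SMC review if, during the 7 days after product administration". Its first item is "One (1) or more participants experiences an SAE that is unexpected and associated with study product administration". The three 10% grade 3 rules and the bronchospasm/anaphylaxis and allergic/injection-site items share the same 7-day limit.
- The second applies at any time. It covers "Any patterns of laboratory values or clinical symptoms that the CI considers to be a significant safety issue for participants", rheumatic carditis or rheumatic fever by the Jones criteria, and named ECG or ECHO findings. It has no SAE item.

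The section closes by saying that later reviews of serious, unexpected and related events "may also result in suspension of further study product administrations".

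Section 9.6 adds oversight. "The ISM should be able to access participant records readily in real time" and "The ISM should investigate those events considered serious and unexpected". At its dose reviews, "The SMC will also review the recorded AEs and SAEs". Between scheduled reviews, "the SMC will meet to assess any events that trigger the halting rules or as needed to provide a recommendation and findings".

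Section 5.3.3 allows termination for serious safety concerns. Section 5.3.4 stops further product for the affected participant. Section 9.3.1 requires SAE notification within 24 hours. Item 1 of the Day 56 list in section 7.3 asks only that SMC approval is in place. The adverse-event review on that list concerns the participant about to be dosed.

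**The concern.** The same single event is treated differently according to its timing. Within 7 days of a dose it stops dosing for everyone until the ISM and SMC have reviewed it. In the days between SMC approval and Dose 2 it does not, although a second exposure is then imminent and the scheduled SMC review is already past.

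The risks that the protocol itself names are partly delayed and immune-mediated. Section 2.3.1 raises cross-reactive antibodies, and section 2.1 lists glomerulonephritis among the post-streptococcal sequelae. Rheumatic fever and carditis are covered at any time, but glomerulonephritis is not named there. Suppose a serious case arose on Day 52, before anyone had received Dose 2, and was rated unexpected and associated. No listed event trigger would fire, and a halt would depend on the CI invoking the judgement item. At stake is whether other healthy volunteers in a Phase I trial receive a second dose before that event has been reviewed.

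**Working it through.** No power or error-rate figure is involved. The check is a reading of the rules plus day arithmetic, taking a common Day 0 for all participants.

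**Inputs**
- Length of the SAE trigger: 7 days after a dose (section 9.5).
- SMC Dose 1 review: Day 49±5 (Protocol Summary, schedule).
- Dose 2: Day 56±5 (section 7.3).
- Minimum from SMC review to the next injection: seven days (section 11.4).
- Allocation: 15 vaccine, 5 saline (section 4).

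**Step 1. Windows**
- SMC review: 49 − 5 = Day 44 to 49 + 5 = Day 54.
- Dose 2: 56 − 5 = Day 51 to 56 + 5 = Day 61.

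**Step 2. SMC review to the first Dose 2**
- Shortest: 7 days, by the section 11.4 minimum.
- Nominal: 56 − 49 = 7 days.
- Longest: 61 − 44 = 17 days.

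**Step 3. Is the SAE trigger active then?**
- The 7 days after Dose 1 end on Day 7. The earliest SMC review is 44 − 7 = 37 days later, and the nominal one is 49 − 7 = 42 days later.
- The trigger is therefore inactive from SMC approval until the first Dose 2 is given. It then becomes active again for 7 days after each Dose 2.

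**Step 4. Staggered second doses**
- Dose 2 visits can be 61 − 51 = 10 days apart. An SAE on days 8 to 10 after the earliest Dose 2 could fall outside the trigger while others still wait, unless another participant's dose has reopened it for that participant.

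**Step 5. Who could be re-exposed**
- If one vaccine recipient has the event: 15 − 1 = 14 other vaccine recipients. The 5 saline recipients would receive saline again.

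**Step 6. Does another provision compel a hold?**

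| Provision | Effect on the other participants |
| --- | --- |
| 9.5, CI item | Halts if the CI considers a pattern to be a significant safety issue |
| 9.5, closing paragraph | Suspension is possible after review |
| 9.6, ISM | Access and investigation; no instruction to hold dosing |
| 9.6, SMC | Must meet if a halting rule fires, otherwise as needed |
| 5.3.3 | Termination is possible |
| 5.3.4 | Affected participant only |
| 9.3.1 | Notification only |
| 7.3, Day 56 item 1 | Checks the approval already given |

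Every entry that could stop the others needs a judgement. None is automatic for this event.

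**The case against.** The strongest reply is that section 9.5 is a deliberate two-tier design: a fixed rule close to dosing and review-based suspension later. Its closing paragraph names this very kind of event. The 7-day trigger also needs judgement, because the SAE must be rated unexpected and associated. Under section 9.2.1, associated means temporally related with no other explanation. A CI who reaches that view six or more weeks after Dose 1 could hardly deny a significant safety issue. Once the CI says so, the at-any-time item is itself a halting rule, its halt is mandatory, and the SMC must meet. The trial has one site and 20 participants, SAE notification within 24 hours, and an ISM who sits on the SMC. The SMC charter is not shown and may deal with late SAEs.

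Much of this stands. A reader might infer that late SAEs are unaddressed, or that only an as-needed SMC meeting remains. The text does not support that, because the CI item can fire and would bring the SMC in. Nor does it support a gap lasting until the last Dose 2, since the trigger is active again once the first Dose 2 is given. No gap is claimed before the SMC review either, because recorded SAEs can reach that meeting directly or through the ISM.

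What does not fall away is the difference in kind. Rating an event as associated is one decision and stopping everyone's dosing is a second. Within 7 days the second follows by rule. Afterwards it does not, and the CI item speaks of patterns, which may not clearly fit one event.

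**Conclusion.** The point holds in this limited form. From SMC approval to the first Dose 2 (nominally 7 days, at most 17), and beyond day 7 after an early Dose 2, an unexpected, associated SAE outside the rheumatic and ECG/ECHO triggers stops dosing only through someone's judgement. At most 14 other vaccine recipients could be re-exposed.

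It would be tempting to say that all 19 others, or everyone, would be re-exposed. That is wrong, because 5 participants receive saline. It would also be tempting to extend the bronchospasm/anaphylaxis trigger in the same way. Nothing in the protocol suggests that such a reaction to Dose 1 is plausible six or more weeks later.

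The importance is minor: the interval is short, safeguards exist, and a late event must still be attributed to the vaccine. The protocol gives no event rate, so no probability is claimed. The conclusion assumes that the SMC charter does not already impose a hold.

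**What to change.** - In section 9.5, state that an unexpected, associated SAE at any time from Dose 1 until the last participant has received Dose 2 halts study product administration pending expedited ISM/SMC review. Leave the other 7-day triggers unchanged.
- In item 1 of the Day 56 list in section 7.3, add a check that no such SAE has occurred in any participant since SMC approval without ISM/SMC clearance.
- State that the seven-day minimum in section 11.4 applies to the scheduled Dose 1 review and not to this expedited clearance. Otherwise a review after Day 61 − 7 = Day 54 would by itself push Dose 2 past its window.

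No new data are needed, because SAEs are already notified within 24 hours. The cost is a possible extra expedited review and a delay to Dose 2, which could still exceed the Day 61 limit if clearance takes long.

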**Day 0, (Day of Dose 1)**

Two participants, one randomized to receive vaccine study product and the other control saline will have study product administered 24 hours prior to the remaining 18 participants which may be split into 2 cohorts. The safety of the first dose in these two participants will be initially observed for at least 6 hours and evaluated by the clinical investigator and the ISM to make recommendation on whether to proceed with administration of the study product to the remaining 18 participants.

These 2 participants will follow the events listed in Day 0 and will be dosed on Day 56 as all the participants of the study.

The safety of the first dose of the vaccine candidate in the study participants will be evaluated by a SMC that will make a recommendation to proceed to the administration of the next vaccine dose. See section 4 for the vaccine candidate dosage schedule. Refer to Appendix A for a tabular presentation of the study procedures.

Procedures to be followed at enrollment:

1. Review study eligibility and record concomitant medications.

2. Review medical history for any change in status from screening

3. Record baseline symptoms and vital signs. If the participant is febrile (temperature >38°C [>100.4F] or has an acute illness, the dose must be rescheduled. If rescheduled, the study product administration must be within 28 days after all screening procedures.

4. Targeted physical examination including cardiac auscultation. Particular attention to any elicited symptoms and signs consistent with rheumatic fever i.e. rash, arthalgia/arthritis (joint pain/swelling), renal angle tenderness and cardiovascular examination and movement disorder.

5. Obtain a throat swab and conduct a rapid antigen test for group A streptococci

6. Collect urine for urinalysis and blood for hematology, biochemistry and serology including, ASOT, α-DNase B, detection of α-J8 peptide vaccine specific antibodies, blood sample for quantitative cellular response as well as serum samples for α-DT antibodies and safety serum storage (refer to appendix D for tests required and blood volumes).

7. For female participants ensure that adequate contraceptive precautions have been taken since the screening pregnancy test and ensure that a urine test for -HCG is negative.

8. Perform breath alcohol test and urine drug screen.

9. Administer the study product.

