| **Local reaction to study product** | **Mild**  **(Grade 1)** | **Moderate (Grade 2)** | **Severe**  **(Grade 3)** | **Potentially Life Threatening (Grade 4)** |
| --- | --- | --- | --- | --- |
| Pain | Does not interfere with usual activities | Repeated use of non narcotic pain reliever  > 24 hours or interferes with activity | Any use of narcotic pain reliever or prevents daily activity | Emergency room (ER) visit or hospitalization |
| Tenderness | Mild discomfort to touch | Discomfort with movement | Significant discomfort at rest | ER visit or hospitalization |
| Erythema/  Redness | 2.5 - 5 cm | 5.1 – 10 cm | > 10 cm | Necrosis or exfoliative dermatitis |
| Induration/Swelling | 2.5 - 5 cm and does not interfere with activity | 5.1 – 10 cm or interferes with activity | > 10 cm or prevents daily activity | Necrosis |

| Systemic reaction to injectable product | **Mild**  **(Grade 1)** | **Moderate (Grade 2)** | **Severe**  **(Grade 3)** | **Potentially Life Threatening (Grade 4)** |
| --- | --- | --- | --- | --- |
| Fever (°C)^  (°F) | 38.0 – 38.4  100.4 – 101.1 | 38.5 – 38.9  101.2 – 102.0 | 39.0 – 40  102.1 - 104 | > 40  > 104 |
| Other solicited events | Does not interfere with usual activities | Repeated use of non narcotic pain reliever  > 24 hours or interferes with activity | Any use of non-narcotic pain reliever or prevents daily activity | Emergency room (ER) visit or hospitalization |
| Unsolicited events | Should be graded according to the criteria in Appendix B | | | |

Adverse events characterized as intermittent require documentation of onset and duration of each episode.

All unsolicited AEs must be graded for severity and relationship to study product (see below and Appendix B).

Information collected will include the type of the AE, the onset and the severity of the AE (see table above and appendix B). All changes in the severity of an AE should also be recorded on source documents or medical records to document the duration of the AE at each level of intensity. Adverse events characterized as intermittent require documentation of onset and duration of each episode.

If the CI has any doubt as to whether a clinical observation is an AE, the event will be recorded in the appropriate CRF.

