## Planned Interim Analyses

### Safety Review

Approximately seven weeks after the first product administration, the Safety Monitoring Committee (SMC) will review study data accumulated up to the five-week time point. The SMC is responsible for monitoring participant safety in this QIMR sponsored study. The SMC will review factors that might compromise the study, such as protocol deviations, and losses to follow-up, and the accumulated safety data.

The data presented to the SMC will not be separated by treatment group. Specifically, data from saline and vaccine candidate recipients will be pooled. SMC members may request additional unblinded analyses at their discretion. The SMC will make recommendations to the Chief Investigator and QIMR as to whether the study should continue, be modified, or terminated, and specifically, whether corrective actions are required, or the study may proceed as planned to the second dose of product.

In the SMC report, the demographics of study participants: age, gender, race and ethnicity; will be tabulated. A table of study completion status will display the counts of participants who are in follow-up, have terminated, or have completed the trial by study group. All subjects dropped from the study will be listed, with the date of termination, length of time on study, and reason for termination. Participant specific protocol deviations will be tabulated according to category and reason for deviation.

Reported safety data will include unsolicited adverse event reports, reactogenicity solicited at one-week post-product administration; hematology, chemistry, and urinalysis at four weeks post-product administration. Additionally, analyses will be conducted with ECG, ECHO at four weeks post-product administration and at the final study visit.

Adverse events will be classified and counts will be expressed in terms of the number and percentage of participants experiencing the event.

Local and systemic reactogenicity will be classified by reaction type, and the maximum grade over the follow-up period for each participant will be reported. The frequency of occurrence and severity of reactogenicity assessments will be summarized in tables and bar-charts.

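### The three percentage halting rules name only Grade 3, so on a maximum-grade count some Grade 4 reactions would not count toward the 10% trigger during staggered dosing (minor wording error)

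*Protocol*

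**What the plan says.** Section 9.5 (Halting Rules) has three percentage triggers, each set at 10% of those enrolled so far. The fever rule reads "10% or more of the participants enrolled to date experience a severe (grade 3) study product associated fever". The rules for local redness or induration and for subjective reactions (pain, headache, malaise, myalgia) name the same grade. None adds *or higher*.

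The tables in Section 9.2.1 place a further grade above severe. Grade 4 fever is above 40°C, against 39.0 to 40°C for Grade 3. Grade 4 pain and other solicited events are defined by "Emergency room (ER) visit or hospitalization". Grade 4 redness is "Necrosis or exfoliative dermatitis", and Grade 4 induration is necrosis.

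Section 9.5 does not say how a participant whose grade changes is counted. Two other places bear on this:

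- Section 9.2.1 asks that changes in severity be recorded "to document the duration of the AE at each level of intensity".
- Section 11.9.1 says that, in the report to the Safety Monitoring Committee (SMC), "the maximum grade over the follow-up period for each participant will be reported".

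Section 9.5 also has single-case triggers. One is "One (1) or more participants experiences an SAE that is unexpected and associated with study product administration". Another covers allergic events and ulceration, abscess or necrosis at the vaccine site. The clinical investigator (CI) may also halt the trial at any time over findings judged a significant safety issue.

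**The concern.** Read literally with one maximum grade per participant, a worse reaction fails to count toward a trigger that a milder one meets. Three kinds of associated event are affected: a Grade 4 fever, a Grade 4 subjective reaction, and exfoliative dermatitis unless it is classed as an allergic event. Necrosis is not affected, because one case halts dosing under its own rule.

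What is at stake is whether dosing pauses automatically. That matters only where some participants are still waiting for an injection when the event occurs:

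- **Sentinel step.** Two participants are dosed "24 hours prior to the remaining 18 participants which may be split into 2 cohorts". Their review rests on an observation window: "The safety of the first dose in these two participants will be initially observed for at least 6 hours".
- **Split first dose.** The same sentence of Section 7.2 allows the remaining 18 to be dosed in two parts.
- **Dose 2.** The visit window is Day 56 ± 5, and no sentinel step is described for it.

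**Working it through.** The protocol gives no count for the 10% threshold, so there is no stated figure to reproduce.

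**Inputs.** Threshold 10% of participants enrolled to date (Section 9.5). Two sentinels, then 18 (Sections 4, 7.2 and 11.4). N = 20. Dose 2 window Day 56 ± 5 (Section 7.3).

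**Formula.** The smallest count that halts is ceil(0.10 × n).

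- n = 2: ceil(0.2) = 1. For any n up to 10 it is 1.
- n = 11: ceil(1.1) = 2. For n = 11 to 20 it is 2.

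**Value of n.** Section 11.4 enrolls the other 18 after the sentinel step, so n = 2 there. For a split first dose, whose part sizes are not given, I assume the second part is not yet enrolled: n = 2 + k, where k is the size of the first part. The threshold is then 1 for k of 8 or fewer and 2 for k of 9 or more.

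**Counts on a maximum-grade basis.** All events are associated and fall under the same rule.

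| Situation | n | Needed | Maximum grades | Grade 3 only | Grade 3 or higher |
|---|---|---|---|---|---|
| Sentinels | 2 | 1 | one Grade 4 | 0/2, no halt | 1/2 = 50%, halt |
| Split, k = 8 | 10 | 1 | one Grade 4 | 0/10, no halt | 1/10 = 10%, halt |
| Split, k = 9 | 11 | 2 | one Grade 3, one Grade 4 | 1/11 = 9.1%, no halt | 2/11 = 18.2%, halt |
| Dose 2 | 20 | 2 | two Grade 3 | 2/20 = 10%, halt | 2/20 = 10%, halt |
| Dose 2 | 20 | 2 | one Grade 3, one Grade 4 | 1/20 = 5%, no halt | 2/20 = 10%, halt |
| Dose 2 | 20 | 2 | two Grade 4 | 0/20, no halt | 2/20 = 10%, halt |
| Lone event | 11 to 20 | 2 | one Grade 4 | 0, no halt | 9.1% down to 5%, no halt |

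**Timing.** If sentinel observation lasts exactly 6 hours, 24 − 6 = 18 hours pass before the next injections. Dose 2 may run from Day 51 to Day 61, so first and last injections can be up to 10 days apart.

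**Alternative convention.** If every recorded grade counts and each Grade 4 participant has a documented Grade 3 phase, the Grade 3 column gives the same result as the last column in every row.

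**Does the SAE rule catch the missed events?** It needs an event that is serious, unexpected and associated.

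- The severity definitions following Section 9.2.1 explain the Grade 4 label as immediate risk of death, and Section 9.2.2 uses the same explanation for its life-threatening criterion. A Grade 4 event that carries that risk is therefore a listed SAE, and one case halts dosing if it is also unexpected and associated.
- The grading tables, however, assign Grade 4 by a temperature or an emergency visit alone. Neither establishes immediate risk of death.
- The hospitalization criterion in Section 9.2.2 covers only prolonged inpatient stays. Its last bullet, which contains the emergency-room example, is left to medical judgement.

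**The case against.** A reader might infer that a Grade 4 reaction cannot halt this trial, or that the most severe events are unguarded. The documents do not support that. The case against giving the point much weight is strong:

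- **The Grade 4 label points to the SAE rule.** Where the label and its definition agree, one unexpected, associated case halts dosing, which is stricter than 2 of 20. This stands for events that do threaten life. It does not settle those graded by temperature or an emergency visit alone. Section 2.3.1 also lists fever, headache and local pain among possible reactions, so whether such an event is unexpected could be argued, although no life-threatening form is described there.
- **Discretionary cover exists.** The CI can halt at any time. Section 9.6 gives the independent safety monitor (ISM) ready, real-time access to records and requires the CI to keep the ISM informed. This stands, but percentage rules exist so that a pause does not depend on discretion.
- **Maximum-grade counting is not in Section 9.5.** It appears only for SMC tables, and Section 9.5 speaks of participants who experience a grade. Section 8.1 asks participants to report reactions of Grade 3 and upward, where Section 4 names only Grade 3, which suggests a minimum grade was meant. This stands. It makes the defect one of ambiguity and shows that inclusive wording was available.
- **The reach is small.** Reactions in the sentinel window are reviewed by the CI and ISM whatever their grade. Later sentinel events have no scheduled contact before the Day 2 ± 1 call, so a halt would usually depend on self-report. Once all 20 have had dose 1, SMC approval is required before dose 2 (Sections 7.3 and 9.6), so the wording can then only delay expedited review. This stands.

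**Conclusion.** The point holds as a minor wording error in a stated safety trigger. The uncovered case is narrow: an associated Grade 4 event set by temperature or an emergency visit alone, or exfoliative dermatitis not classed as allergic, that is not treated as an unexpected SAE and does not lead the CI to halt. It affects dosing only after the sentinel observation window, in a split first-dose group, or within the Day 56 ± 5 window.

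Within that case the wording can reverse the decision, as the sentinel, split-cohort and dose 2 counts show. The conclusion assumes counting by maximum grade and, before full enrolment, that participants not yet dosed are not counted as enrolled. If all 20 counted from the start, the threshold would be 2 throughout, and a lone sentinel event would not halt under either wording. The protocol gives no Grade 4 rates, so no probability is attached.

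**What to change.** In each of the three percentage rules of Section 9.5, write *grade 3 or higher*. The count is then the same under either convention. This does not make a lone Grade 4 event halt dosing once 11 to 20 are enrolled. If the sponsor wants that, it needs a separate single-case rule, which is a design decision and not a wording correction.

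As a separate correction, reword the hospitalization criterion in Section 9.2.2 to cover any inpatient admission or the prolonging of an existing one. Its last bullet already treats hospitalization without that qualifier.

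The cost is a few words of amendment, with matching text in the SMC charter and SAE form. The downside is an occasional extra review pause and a few more SAE reports.
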